#### Primary objective

To develop, refine, implement and evaluate an optimised, sustainable and scalable implementation model for improving population-based coverage of pneumonia management among under-five children, in alignment with the GoI’s Childhood Pneumonia Management Guidelines.^4^ The model aims to achieve ≥80% treatment coverage in the target population.

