**Figure 2 F2:**
[figure not shown]
Sample size estimation.

The total number of children to be surveyed is calculated based on a prevalence rate of 5%, resulting in an estimated sample size of 2400.^5^ Considering the proportion of 5-year-olds in the population (12% based on census data) and the average household size (4.8 as per the NFHS 5 report for Haryana), the number of households to be covered is calculated as 4167 households.^17^ These households will be selected using Probability Proportional to Size (PPS) sampling methods from the defined study area served by the 10 HWCs.^18^ Since community-level healthcare workers maintain a list of under-five children in each household, systematic random sampling will be used to select children within the chosen households.

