### Intervention package

The intervention package will be aligned with the GoI guidelines, which include early identification of pneumonia cases through ASHAs and empowering families, prompt care-seeking from appropriate providers for pneumonia treatment and prompt referral of severe pneumonia cases with pre-referral treatment. At the outpatient department (OPD) of facilities (HWCs/PHCs/CHCs/DH), treatment providers need to be available, be competent and have access to appropriate logistics (equipment, regular supplies of medicines). Pulse oximeters will be provided at the OPDs of these facilities to assess oxygen saturation for improved assessment/evaluation of severe cases requiring referral.

For children, (0–59 days) with PSBI, a prereferral dose of gentamicin and amoxicillin will be provided by the health workers at the HWCs, and then cases are referred to higher facilities. But if a referral is not possible/denied, the package also aims to provide treatment to children aged 0 to 59 days in the outpatient department of primary-level care. In cases where caregivers are unable to bring their infants to the health facilities for the full course of injection, gentamycin and oral amoxicillin for 7 days will be provided by the auxiliary nurse midwives to cases (0–59 days) at home.^4 19 20^

In discussions with the government, strategies will be finalised to promote treatment in female children, such as providing additional incentives to ASHAs for referring or accompanying girl children for pneumonia treatment, free transportation for girl children to facilitate referral for outpatient treatment and providing free food or compensating daily wages lost due to hospital admissions.

At the post-facility level, ASHAs will be rewarded (with government consensus) for ensuring full compliance with the treatment course in female children. The decision to address the appropriate treatment of pneumonia in the private sector, where many children with pneumonia seek care, by involving private providers in the discussion with the government partners, will be based on the formative research findings. Appropriate use of bronchodilators in children with wheeze at health facilities and identification of conditions mimicking pneumonia for rational therapy will also be included. Finally, recognition of cases that do not have pneumonia and do not require antibiotics but may benefit from supportive treatment.

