### Research teams

There will be three teams: (i) the Implementation Support Team (IST), (ii) the Programme Learning Team (PLT) and (iii) the Outcome Measurement Team (OMT).

The IST will provide technical support to government partners and assist in programme implementation. They will facilitate government staff training in the study area, identify process gaps for refinement and develop tools and job aids. Additionally, the IST will support community awareness activities and data collection from ASHA records and healthcare facilities.

The PLT, composed of qualitative researchers, will assess fidelity and compliance through methods like focus group discussions (FDGs), in-depth interviews (IDIs) and observations. They will provide prompt feedback to the IST and deliver weekly reports.

The OMT will focus on measuring primary and secondary outcomes. They will conduct baseline and endline cross-sectional surveys in randomly selected households within the study area, assessing population-based programme coverage using a randomised sample selection method.

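### Survey children are selected from lists kept by community health workers, with no independent enumeration described, so coverage against the 80% criterion risks being overstated

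*Protocol article*

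**What the plan says.** The Sample size section describes two stages. Households come first: "These households will be selected using Probability Proportional to Size (PPS) sampling methods from the defined study area served by the 10 HWCs". Children come second: "Since community-level healthcare workers maintain a list of under-five children in each household, systematic random sampling will be used to select children", within the households chosen at the first stage. The list is given as the basis for the second stage only.

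Under Research teams, a separate Outcome Measurement Team does the fieldwork: "They will conduct baseline and endline cross-sectional surveys in randomly selected households within the study area". Its task is described as "assessing population-based programme coverage using a randomised sample selection method".

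The Primary objective sets an absolute target: "The model aims to achieve ≥80% treatment coverage in the target population". The section on describing and tracking outcomes also defines success as at least 80%.

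The Intervention package relies on community workers. It includes "early identification of pneumonia cases through ASHAs and empowering families". One strategy still to be settled with government is "providing additional incentives to ASHAs for referring or accompanying girl children for pneumonia treatment", and the same section adds that "ASHAs will be rewarded (with government consensus) for ensuring full compliance with the treatment course in female children".

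The strengths and limitations box presents the sampling as securing representative data. The limitations given there and in the Discussion concern recall, self-report and the broad case definition. The sampling frame is not among them.

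**The concern.** A frame for measuring population coverage should not depend on contact with the programme being measured. Here, the children who can be selected are those known to community-level workers, and the strategy acts through workers of that type. Newborns, recent arrivals and families with little worker contact are plausible omissions. They are also plausible candidates for lower coverage. If being unlisted and being uncovered share a cause, coverage among listed children exceeds coverage in the population.

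This matters most for the 80% criterion. It is an absolute threshold, so nothing cancels, and the error does not shrink as the sample grows. The pre-post difference is also exposed if list completeness changes while the intervention alters the workers' activity.

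**Working it through.** **1. The plan's own figures.** Inputs from the Sample size section: 120 cases, 5% prevalence, 12% of the population under five, 4.8 persons per household.

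- Children: 120 / 0.05 = 2400.
- Households: 2400 / (4.8 × 0.12) = 2400 / 0.576 = 4166.7, rounded up to 4167.

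Both published figures reproduce. In reverse, 4167 × 4.8 × 0.12 = 2400, so the calculation takes every under-five in every selected household, about 0.58 per household. Selecting only some of them would give fewer than 2400 children. The within-household selection step therefore conflicts with the arithmetic that set the number of households.

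**2. Effect of unlisted cases on measured coverage.** Let m be the share of eligible cases not on the lists, and c the coverage among those cases. With 80% among listed cases:

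true coverage = (1 − m) × 0.80 + m × c, and overstatement = m × (0.80 − c).

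The article gives neither m nor c, so both are assumptions. The value c = 25% borrows the current coverage stated in the Sample size section, c = 50% is intermediate, and c = 80% means unlisted cases fare the same as listed ones.

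| m | c = 25% | c = 50% | c = 80% |
|---|---|---|---|
| 5% | 0.7600 + 0.0125 = 77.3% | 0.760 + 0.025 = 78.5% | 80% |
| 10% | 0.720 + 0.025 = 74.5% | 0.72 + 0.05 = 77.0% | 80% |
| 20% | 0.64 + 0.05 = 69.0% | 0.64 + 0.10 = 74.0% | 80% |

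The overstatement runs from 0 to 11 points over this grid.

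**3. Listed coverage needed for a true 80%.** Solving for listed coverage gives (0.80 − m × c) / (1 − m). With c = 25%:

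- m = 5%: 0.7875 / 0.95 = 82.9%
- m = 10%: 0.775 / 0.90 = 86.1%
- m = 20%: 0.75 / 0.80 = 93.8%

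**4. Comparison with sampling error.** At 80% and n = 120, the two-sided 95% half-width under simple random sampling is 1.96 × √(0.80 × 0.20 / 120) = 7.2 points. In the grid, only the cell with m = 20% and c = 25% exceeds this. The interval reflects sampling error only and does not include the frame error.

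**5. Pre-post change.** Suppose listed coverage rises from 25% to 80%, an observed change of 55 points. With m = 10% and unlisted cases at 25% in both surveys, true coverage goes from 25% to 74.5%, a change of 49.5 points. If unlisted cases move with listed ones, there is no bias.

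**The case against.** The strongest reply is that the list enters late. Households are drawn from the study area and visited by a team separate from the implementers. At about 0.58 under-fives per household, there is little left to select. The article does not say that an unlisted child found at the door would be turned away, and the full protocol or field manual may describe a roster. This narrows the concern but does not remove it: the article names the worker list as the basis for selecting children, and a selection made from that list cannot reach a child who is not on it.

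The direction is also not certain. The primary outcome counts care from any qualified source, private clinics and hospitals included, and the strategy also works through caregiver awareness and facility readiness. Little contact with a worker need not mean no coverage. That stands, and it is why a zero-bias column belongs in the table. A stable listing gap would also partly cancel in the pre-post difference, though not against the absolute 80% criterion.

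A reader might infer three stronger things that the documents do not support:

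- **Pneumonia cases that workers fail to detect leave the denominator.** They do not. The lists are of under-five children, not of detected cases, so a listed child with undetected pneumonia still counts.
- **Workers are paid in a way that distorts the lists.** The article does not say that the list-keepers are ASHAs. The rewards depend on government agreement, concern girls, and are tied to referral or treatment compliance, not to listing or survey results.
- **The article's own population figures prove under-listing.** The Study setting gives 9897 under-fives in 107,440 people (9.2%), whereas 12% would be 12,893. Nothing says that 9897 comes from worker lists.

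**Conclusion.** The point holds as a risk. The plan selects children from lists kept by the type of worker the intervention acts through, describes no independent enumeration, and applies an absolute population threshold to the result. Upward bias is the likelier direction. A reader might conclude that coverage is in fact overstated, but the article gives neither list completeness nor coverage among unlisted children, so that cannot be shown.

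Under the stated assumptions (80% among listed cases, 5% to 20% of cases unlisted, unlisted coverage between 25% and 80%), the overstatement is between 0 and 11 points. With 10% or fewer unlisted it is at most 5.5 points, less than the sampling half-width. It would then change the conclusion only if the observed figure lay fairly close above 80%. The conflict between selecting some children and an arithmetic that counts all of them needs no assumption beyond the plan's own figures.

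**What to change.** In each sampled household, the outcome team should roster every resident under-five, include all of them, and record whether each is on the worker list. The 80% criterion should be judged on all rostered children, and the proportion found on the lists should be reported.

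Baseline data were collected between June and August 2023 (Study status), so changing the frame at endline alone would introduce a difference between surveys. The pre-post comparison should therefore also be reported for listed children only, which applies the same selection rule at both times. It does not correct for a change in list completeness.

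Endline was scheduled for February to April 2025. If that fieldwork is complete, the report should state the frame actually used, name it as a limitation, and show how the 80% conclusion changes over a range of unlisted shares and coverage values, as in the table above.

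The cost is a little interview time at visits already planned, plus revised sampling wording. If fieldwork is complete, it is a short sensitivity table and a limitation statement.

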**Method and analysis:**

This implementation study uses a quasi-experimental pre-post design and a mixed-methods approach, conducted in three phases: (i) formative research, (ii) model optimisation through iterative testing in a learning block and (iii) scale-up and concurrent evaluation. The study is set in Palwal district, Haryana, and the primary catchment/study area will be the Health and Wellness Centres, the most accessible public health facilities for the community. Approximately 4167 households will be surveyed to capture ~2400 under-five children, among whom about 120 pneumonia cases (based on an estimated 5% prevalence) will be included in the analysis of treatment coverage and outcomes. Quantitative data will be analysed using descriptive statistics and generalised linear models, while qualitative data from focus group discussions and in-depth interviews will be thematically analysed using NVivo software.

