### Sample size

A recent study in the same district found that the prevalence of pneumonia among under-five children in the last 2 weeks was around 5%.^15^ Currently, approximately 25% of under-five children seek appropriate care for ARI, indicating a programme coverage of around 25%.^5 16^ With the introduction of the new implementation strategy, we expect an increase in pneumonia treatment coverage by 80%. To account for potential non-response and to estimate 80% coverage of appropriate treatment at baseline and end-line surveys for under-five children with pneumonia cases (as per the operational definition), a conservative sample size of 120 is to be included. Additionally, based on these assumptions, the estimated sample size at a 5% level of significance for each survey (baseline and end-line), and a varied range of coverage is shown in figure 2.

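### The 4167 households yield 2400 children only if every under-five in them is enrolled, yet the plan then samples children within those households

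*Protocol article*

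**What the plan says.** The size of each survey is set in Methods and analysis, Sample size. For children with pneumonia, "a conservative sample size of 120 is to be included". The next step is "The total number of children to be surveyed is calculated based on a prevalence rate of 5%, resulting in an estimated sample size of 2400". Then, using a 12% share of under-fives in the population and a mean household size of 4.8, "the number of households to be covered is calculated as 4167 households".

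Selection follows in the same paragraph. "These households will be selected using Probability Proportional to Size (PPS) sampling methods" from the area of the ten Health and Wellness Centres. Because health workers keep lists of under-fives by household, "systematic random sampling will be used to select children within the chosen households". No interval, fraction or number of children per household is given.

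The Abstract (Method and analysis) repeats the conversion without the second stage: "Approximately 4167 households will be surveyed to capture ~2400 under-five children". The strengths list attaches the systematic step to households rather than to children, and the Research teams section speaks only of households drawn at random.

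**The concern.** The number of households and the rule for choosing children describe two different surveys. The calculation counts every under-five in a selected household. The selection sentence describes a further stage that takes only some of them. If that stage is real, the households planned are too few for the children planned, and so for the cases on which coverage is estimated.

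The rule also decides who enters the denominator of the primary outcome. A reader cannot tell whether all under-fives in a household are eligible, one of them, or every k-th child on a list. If field teams read the sentence differently at baseline and endline, the pre-post comparison would set two sampling schemes against each other.

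**Working it through.** **Inputs (all from Sample size).** Target cases 120; prevalence 5%; under-five share 12%; household size 4.8; households 4167.

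**1. Reproduce the plan's figures.**
- Children: 120 / 0.05 = 2400.
- Mean under-fives per household: 0.12 × 4.8 = 0.576.
- Households: 2400 / 0.576 = 4166.7, rounded up to 4167.
- Back-check: 4167 × 0.576 = 2400.2.

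The figures agree. The factor 0.576 counts all under-fives, and no within-household fraction enters the conversion.

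**2. Add a within-household stage with fraction f.** Expected children = 2400f, cases at 5% = 120f, households needed for 2400 children = 2400 / (0.576f). The values of f are assumptions.

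| f | Children | Cases | Households needed |
|---|---|---|---|
| 1 (all children) | 2400 | 120 | 4167 |
| 0.9 | 2160 | 108 | 4630 |
| 0.8 | 1920 | 96 | 5208 |
| 0.5 | 1200 | 60 | 8333 |

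**3. One child per household (assumed rule).** The yield is the number of households that have any under-five, 4167 × 0.576 / a, where a is the mean number of under-fives in such households. The article does not give a, so a range is shown.
- a = 1.1: 2182 children, 109 cases.
- a = 1.2: 2000 children, 100 cases.
- a = 1.5: 1600 children, 80 cases.
- Poisson counts with mean 0.576: share of households with a child = 1 − exp(−0.576) = 0.438, giving 1825 children and 91 cases.

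Reaching 2400 children would then take 4583 (a = 1.1) to 6250 (a = 1.5) households; Poisson 5481.

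**4. Precision.** The 95% half-width at 80% coverage is 1.96 × √(0.8 × 0.2 / n), ignoring clustering: 7.2 points at n = 120, 8.2 at n = 91, 8.8 at n = 80.

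**5. Children with siblings.**
- One-child rule, Poisson counts: children from single-child households are exp(−0.576) = 56% of all under-fives, but 0.576 × exp(−0.576) / 0.438 = 74% of the sample.
- Equal-probability systematic draw from a list of children: every child has the same chance, so siblings are not under-represented. The yield is still 2400f.

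**The case against.** The strongest reply is that the sentence is condensed wording for how children are listed and found, and that all of them are taken. The Abstract reads that way, and at 0.58 under-fives per household there is little to sample. This is plausible, and it is why two stronger readings do not stand.

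- A reader might infer that 2400 cannot be reached. The document does not show that: the fraction is unstated, and 0.576 is a mean, so the realised count may differ. What stands is that the expected yield falls below 2400 as soon as any child is left out by design.
- A reader might infer that siblings are under-represented. That needs a one-child or fixed-number rule, and the article states neither. The mention of health workers' lists fits an equal-probability draw just as well.

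A second reply concerns cases. The 5% is a two-week figure, while the operational definition looks back 28 days, so more cases per child may be found. With 1825 children, a 28-day prevalence of 120 / 1825 = 6.6% would give 120 cases; with 1600 children, 7.5%. This is fair, and it makes the case shortfall conditional on the plan's own 5%. It does not change the number of children.

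Third, the 120 is called conservative and already allows for non-response. But that allowance sits inside the 120. Using it to absorb subsampling would spend it on something else.

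Finally, detailed field procedure and weighting may be in a fuller document. That would excuse a missing interval. It does not excuse a printed rule that conflicts with the printed calculation.

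**Conclusion.** The inconsistency holds. The calculation assumes full inclusion with no surplus, the selection rule describes sampling, and no genuine subsampling of the 4167 households is compatible with an expected 2400 children.

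The size depends on a fraction that is not stated: 2400f children and 120f cases at 5%. The range of 1600 to 2180 children and 80 to 109 cases rests on an assumed one-child rule with 1.1 to 1.5 under-fives per household that has any. The Poisson figures of 1825 and 91 fall inside it. The loss of precision would be modest, from 7.2 to at most 8.8 points over that range before clustering. Distortion by sibling number is a possible consequence of one kind of rule, not a demonstrated fault.

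**What to change.** Replace the within-household sampling with inclusion of all listed under-fives in each selected household. That is what the step from 2400 children to 4167 households already assumes. Allow for clustering within household in the variance.

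If a within-household rule was already used at baseline (June to August 2023), keep it at endline and state it, restate the expected numbers of children and cases, and weight by the inverse selection probability where that probability varies. An equal-probability draw from a child list needs no extra weight for this stage. A one-child rule needs each child weighted by the number of under-fives in the household. As endline fieldwork was scheduled for February to April 2025, the practical form may be to report the rule used in each survey, the numbers obtained and the weights.

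The cost is about one sentence. Beyond that, it is either a few more symptom screens in households with two or more under-fives, or a slightly less favourable stated sample size. Weighting also requires that the number of under-fives per household was recorded.

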### Outcomes

The primary outcome of the study is to find the coverage of effective pneumonia management (ie, management done as per the childhood pneumonia management guidelines of India) from appropriate sources. Appropriate sources refer to government and/or private healthcare facilities like HWCs, PHCs, CHCs, DHs, private clinics/hospitals, etc, where treatment is provided by qualified healthcare practitioners. In contrast, non-appropriate sources include unlicensed practitioners, chemists, traditional or religious healers, and others who are non-registered medical healthcare workers. The secondary outcomes are total recovered cases after 7 days of treatment, treatment failure, compliance to management as recommended by healthcare providers, in-patient case duration and treatment provided, and gender-wise distribution of diagnosed, treated and complaint cases.

